#### Alteration of Infusion Rate

Sinus tachycardia or arrhythmias are known side effects of intravenous salbutamol administration. If a patient receiving a trial drug infusion is noted to have tachycardia (heart rate > 140 beats min^-1^) or any new arrhythmia occurs, the dose rate of drug will be adjusted according to the flow diagram (figure 1). Dose adjustments for renal or hepatic failure will be driven by the cardiovascular response to the infusion rather than on the degree of renal or hepatic impairment. Standard anti-arrhythmic therapy will be given if indicated in addition to alteration of infusion rate.

**Figure 1 F1:**
[figure not shown]
Tachycardiac/arrhythmia management protocol

#### Infusion Termination Criteria

Termination of the infusion is defined as discontinuation of the trial drug infusion without intention to restart the infusion at a later time. Trial drug infusion will be terminated in the following circumstances: death; heart rate >140 beats min^-1 ^despite two adjustments in infusion rate; new arrhythmias despite adjustment in infusion rate; development of a significant lactic acidosis, which in the opinion of the treating clinician is attributable to infusion of the trial drug; 24 hours after discontinuation of mechanical ventilation (of any sort); discharge from ICU; discontinuation of active treatment; request to withdraw from the personal or professional legal representative; decision by the attending clinician that the infusion should be discontinued on safety grounds; 7 days (168 hours) after randomization.

### Clinical Management of Patients in the Trial

Patients involved in the BALTI 2 trial will be managed according to best practice established locally on each unit. Particular care to monitor electrolytes (K^+^, Mg^++^) and glucose is required, with electrolyte supplementation/insulin administered as clinically indicated. The only specific trial requirement is that patients are not routinely administered nebulised beta agonists or other intravenous beta agonists such as isoprenaline. The uncontrolled use of nebulised bronchodilators in the control group will limit the ability of the trial to detect a significant difference in outcomes and the use in the treatment group exposes the patients to a risk of toxicity. There is no definitive evidence at the current time that routine nebulisation of bronchodilators improves outcomes in patients with acute lung injury. In the event of acute bronchospasm, where the clinician feels that a nebulised bronchodilator is required, nebulised ipratropium bromide may be given. If nebulised ipratropium is insufficient to treat the bronchospasm, then salbutamol may be given as a rescue therapy. This will be recorded on the relevant case report form.

There are no specific guidelines for ventilatory management. Clinicians will be encouraged to use a low tidal volume strategy of ventilation based on ideal body weight. Rescue therapies such as high frequency oscillatory ventilation, nitric oxide and extracorporeal membrane oxygenation can be used according to local policy.

### Post Infusion Follow-up

Any patients who remain in the Intensive Care Unit or High Dependency Unit for more that seven days post randomisation (the end of the expected drug infusion period), will continue to be monitored on daily basis until discharged to a ward. The date and place of hospital discharge will be obtained from hospital records.

All patients discharged from hospital will be followed-up six and twelve months after randomisation by postal questionnaire. The questionnaire will collect data on disability and health-related quality of life, using the EQ-5D and SF-12 questionnaires.

### Adverse Event Management

BALTI-2 is recruiting a population that is already in a life-threatening situation, it is therefore expected that many of the participants will experience serious adverse events. Events that are expected in this population and those that are collected as outcomes (e.g. death, organ failure) of the trial will not be reported as SAEs. Other SAEs or SUSARs that occur between trial entry and 30 days after the end of the trial drug infusion will be reported by faxing a serious adverse event log to the trial co-coordinating centre.

### End of Trial

The trial will end when 1334 patients have been recruited and completed twelve month follow-up. The trial will be stopped prematurely if: mandated by the Ethics Committee or the Medicines and Healthcare products Regulatory Agency (MHRA); following recommendations from the Data Monitoring and Ethics Committee (DMEC); funding for the trial ceases.

### Sample size

Published estimates of the mortality rate among ARDS patients range from about 34% to 60%. Two cohort studies that included UK data estimated that hospital mortality was 53.9% [3] (95% CI 49.0, 58.7%) and 60.9% [4] (95% CI 55.9, 65.9%). However, it is likely that mortality has declined since these studies were conducted (1999) because of the introduction of protective ventilation strategies after the publication of a large RCT in 2000. From unpublished ICNARC data for 2005 [5], the hospital mortality among 37,726 patients with ARDS in the UK was 41.2%. The primary outcome for BALTI-2 is 28-day mortality, which is likely to be similar to or slightly higher than hospital mortality because most deaths will occur in ICU within a short period after randomisation, and most patients leave hospital before 28 days. In BALTI-1 the placebo group 28-day mortality rate was 67% (95% CI 0.45, 0.83). A reasonable conservative estimate of the 28-day mortality to be expected in BALTI-2 is 40-50%.

Losses to follow-up for the primary outcome are expected to be very low; in the recently-completed PAC-Man trial 2.4% of recruited patients were lost (mainly because of withdrawal of consent) between randomisation and hospital discharge. We have therefore conservatively assumed a 3% loss of patients for the primary outcome. Table 2 shows the sample sizes necessary for 80% and 90% power to detect a real risk ratio of 0.80 between the salbutamol and placebo arms, using a significance level of 0.05.

**Table 2 T2:** Required sample sizes for 80 and 90% power, RR 0.80, 3% losses

Placebo mortality	Salbutamol mortality	80% power	90% power
40%	32%	1164	1558

42%	33.6%	1076	1440

**44%**	**35.2%**	**998**	**1334**

46%	36.8%	926	1238

48%	38.4%	860	1148

50%	40%	798	1068

We will adopt a target sample size of 1334, which will give 90% power to detect a risk ratio of 0.8 if the placebo group mortality rate is 44%, over 85% power if it is 40%, and more than 90% if it exceeds 44%. The 28-day mortality in the placebo group will be monitored (via the DMEC), to ascertain whether the assumptions made in the sample size calculations are correct. If not, the DMEC will advise on modification to the sample size.

### Statistical Analysis

#### Primary outcome

Mortality at 28 days post-randomisation will be compared between the groups by the risk ratio and 95% confidence interval. Time to death will also be analysed, using survival analysis methods. The groups will be compared using the hazard ratio and its 95% confidence interval from a Cox-proportional hazards model, and a Kaplan-Meier curve will be used for illustration. The proportional hazard assumption across treatment arms will be checked graphically using a log-cumulative hazard plot. This analysis will be repeated when the long term data are analysed, which will include survival to 12 months for all participants. Dichotomous outcomes (death in ICU, death in hospital, tachycardia, arrhythmia and other side effects) will be compared using risk ratios and 95% confidence intervals. For continuous outcomes (duration of ICU and hospital stay, ventilator-free days and organ failure-free days), mean differences and 95% confidence interval will be presented. Time to event outcomes (length of hospital and ICU stay) will be analysed by survival methods and compared using a hazard ratio and 95% confidence interval. The SF-12 physical and mental component scores will be calculated according to the standard methods [1], and compared between the groups by the mean difference and 95% confidence interval. The EQ-5D will be scored according to the UK valuation model [2,3], and presented as the difference in means between the groups with 95% confidence interval.

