### Randomisation

Randomisation will occur via a central telephone randomization service (University of Aberdeen). Randomisation will be minimised by centre, PaO_2_/FiO_2 _ratio (≤6.7, 6.8 to 13.2, ≥13.3kPa), and age (<64, 65 to 84, ≥85 years) because of the expected differences in mortality among these strata. The randomisation service will allocate a numbered treatment pack to each patient. This pack will contain all drugs for giving a complete course of trial treatment to one patient.

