#### Subgroup analyses

Four subgroup analyses are planned to analyse whether the treatment effect is modified by age, severity of hypoxaemia before randomisation, aetiology of ARDS, or APACHE II score. Subgroup analyses will be conducted for the primary outcome only. It is proposed to replace the APACHE II score with the APACHE II mortality risk, which is calculated from the APACHE II score but also takes into account the underlying condition. APACHE II scores do not correlate well with mortality risk as similar scores may occur in patients with different conditions who have different risks of mortality. This means that APACHE II score is unlikely to be predictive of outcome or of treatment effect. The mortality risk incorporates the underlying condition and is a better measure of a patient's "sickness". It is therefore more plausible that mortality risk could have a treatment-modifying effect, and it is preferable to explore this variable's relationship to treatment effect. However, APACHE II score will be retained in the table of baseline characteristics as a descriptor of the population recruited to the trial. For aetiology of ARDS, the ratio of risk ratios in the direct and indirect aetiology subgroups will be calculated, with its 95% confidence interval [6]. We will not attempt any analysis of subtypes of direct and indirect aetiologies because the number of patients available is too small and there is a risk of misleading results. The other three subgroup-classifying variables are continuous. Although the BALTI-2 protocol specified categorisations for these variables, it is proposed to adopt a different approach because there are problems with categorising continuous variables. First, there is no clear biological rationale behind any cut-points, and attempting to use data-driven procedures to derive "optimal" cut-points is liable to be seriously misleading. Second, there is good evidence that any form of categorisation of continuous variables is potentially misleading, and better methods are available [7,8]. For these reasons, the potential treatment-modifying factors will not be categorised. Instead, we will use a regression approach to model the interaction between the continuous baseline variables and outcomes in each group. Categorisations of age, severity of hypoxaemia and APACHE II score will be retained in the table of participants' characteristics, to facilitate comparison of the randomised groups. If there appear to be baseline imbalances that could affect the comparison between the groups, exploratory analyses will be conducted, adjusting for these.

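### Allocation is minimised on factors expected to predict death, but the primary risk ratio names no covariates, so its 95% CI is somewhat too wide and its test mildly conservative.

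*Protocol article*

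**What the plan says.** Three sections of the protocol article bear on this.

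- **Randomisation.** Allocation is minimised by centre, three bands of PaO2/FiO2 and three bands of age. The reason given is "because of the expected differences in mortality among these strata".
- **Statistical Analysis, Primary outcome.** "Mortality at 28 days post-randomisation will be compared between the groups by the risk ratio and 95% confidence interval". A Cox model for time to death is added. Neither analysis has a covariate named.
- **Subgroup analyses, last sentence.** This is the only mention of adjustment for the main comparison: "If there appear to be baseline imbalances that could affect the comparison between the groups, exploratory analyses will be conducted, adjusting for these".

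The word unadjusted is not used. But if adjustment is conditional and exploratory, the primary risk ratio as published is crude.

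**The concern.** Minimisation makes the arms more alike on its factors than simple randomisation would. If those factors predict death, the treatment contrast varies less from one hypothetical repeat of the trial to the next. The usual standard error of a crude risk ratio does not know this and is computed as if patients had been allocated by simple randomisation. The interval then covers more than 95% of the time, and the test rejects less than 5% of the time under the null.

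The article itself declares the factors prognostic, so it takes the benefit of balance in the design and leaves it out of the analysis. The adjustment rule does not repair this. It responds to visible imbalance, which minimisation is meant to make rare for these three factors, and it leaves the covariates to be chosen after the baseline table has been seen.

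At stake is the calibration and efficiency of the primary interval. Bias is not at issue.

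**Working it through.** **Inputs from the Sample size section.** Placebo mortality p0 = 0.44; risk ratio 0.80, so p1 = 0.352; 3% losses ("We have therefore conservatively assumed a 3% loss of patients for the primary outcome"); level 0.05, taken as two-sided because that reproduces the table and matches a 95% CI. About 50 centres (Trial Summary) gives 1334/50, or roughly 27 patients per centre.

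**Step 1: reproduce the plan's figure.** With p̄ = 0.396, per arm:

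n = [1.960·√(2p̄(1−p̄)) + 1.2816·√(p0(1−p0) + p1(1−p1))]² / (p0−p1)²
= [1.960·√0.478368 + 1.2816·√0.474496]² / 0.088²
= (1.3556 + 0.8828)² / 0.007744 = 646.99, so 647.

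Total 1294, and 1294/0.97 = 1334. This matches. The same formula gives 90.0% power at 44% placebo mortality and 85.1% at 40%, as the article states. The sample size is therefore that of a crude comparison of two proportions.

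**Step 2: effect of forced balance.** Let R² be the share of outcome variance explained by the minimisation factors. The documents give no value, so a range is assumed. Put f = √(1−R²), se0 = √(0.478368/647) = 0.02719 and se1 = √(0.474496/647) = 0.02708, and suppose the factors are fully balanced.

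- Adjusted power: Φ[(0.088 − 1.960·se0·f)/(se1·f)]
- Crude power: Φ[(0.088 − 1.960·se0)/(se1·f)]
- Crude type I error: 2[1 − Φ(1.960/f)]
- Interval width, adjusted relative to crude: f

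For R² = 0.10, f = 0.9487. Adjusted power is Φ(1.457) = 92.7%, crude power Φ(1.351) = 91.2%, and crude type I error 2[1 − Φ(2.066)] = 3.9%.

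| Assumed R² | Width ratio | Crude type I error | Crude power | Adjusted power |
|---|---|---|---|---|
| 0 | 1.000 | 5.0% | 90.0% | 90.0% |
| 0.02 | 0.990 | 4.8% | 90.2% | 90.6% |
| 0.05 | 0.975 | 4.4% | 90.6% | 91.4% |
| 0.10 | 0.949 | 3.9% | 91.2% | 92.7% |
| 0.15 | 0.922 | 3.4% | 91.8% | 94.0% |
| 0.20 | 0.894 | 2.8% | 92.4% | 95.2% |

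Before rounding, the gain runs from 0.3 points (R² = 0.02) to 2.8 points (R² = 0.20).

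**Step 3: simulation.** 1294 patients, 50 centres, three bands of each factor, balanced pairs as a stand-in for minimisation, 1200 runs per setting. The crude log risk ratio is compared with a logistic-standardised one adjusted for all three factors. Standard error (SE), standard deviation (SD) and type I error are under the null; power is at risk ratio 0.80.

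| R² | Mean crude SE | True SD of crude estimate | Type I error, crude / adjusted | Power, crude / adjusted |
|---|---|---|---|---|
| 0 | 0.0628 | 0.0629 | 4.5% / 4.8% | 90.1% / 89.6% |
| about 0.05 | 0.0629 | 0.0612 | 4.3% / 5.0% | 90.0% / 90.6% |
| about 0.10 | 0.0628 | 0.0576 | 3.1% / 4.2% | 91.2% / 92.9% |
| about 0.17 | 0.0628 | 0.0568 | 3.3% / 4.8% | 92.4% / 94.9% |

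Monte Carlo error around 5% is ±1.96·√(0.05·0.95/1200), or ±1.2 points. The conservatism is therefore clear at R² of about 0.10 and above, and not separable from chance at 0.05. The adjusted estimate is hardly less variable than the crude one (SD 0.0572 against 0.0576 at R² of about 0.10). The gain comes from a standard error that matches the design, rather than from a steadier point estimate.

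**The case against.** **The crude reading is an inference.** This is a condensed article, and an analysis plan that is not shown may name covariates. That limits certainty. But the article does more than stay silent: it assigns adjustment to a conditional, exploratory role, and that published rule would have to be replaced.

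**The promised power is intact.** A reader might infer that the trial falls short of its stated power. It does not. The Sample size section promises 90% at the design mortality of 44% and a little above 85% should placebo mortality be 40%, and the crude analysis delivers both figures. What is forgone lies above the target.

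**The imbalance rule can still fire.** A reader might infer that it never could for the minimised factors. The bands are coarse: the top PaO2/FiO2 band runs from 13.3 kPa to the eligibility limit of 26.7 kPa, and the lowest age band covers adults up to the early sixties. Imbalance within a band is possible. The rule would rarely respond to these factors, which is not the same as never.

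**The headline is not open to substitution.** A reader might fear that a post hoc adjusted result could displace the primary one. The article labels such analyses exploratory, and nothing in it allows that. The weakness is only that their covariates are chosen after seeing the data.

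**The size is assumed and modest.** This stands. In addition, the simulation used balanced pairs instead of the trial's minimisation algorithm, and fixed centre terms with a very small penalty instead of a random effect, so its figures are indicative.

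**Conclusion.** The point holds as one of efficiency, interval calibration and pre-specification. It does not threaten validity: the crude risk ratio is unbiased and its test errs on the safe side.

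As published, the primary 95% CI is somewhat too wide. For an assumed R² of 0.02 to 0.20, adjustment would narrow it by about 1 to 11% and add about 0.3 to 3 points of power at 44% placebo mortality, with no gain at R² = 0. These figures rest on the assumed R², on near-complete balance from minimisation, and on reading the primary analysis as crude.

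APACHE II mortality risk, which the Subgroup analyses section regards as the better measure of severity, may well predict death too. It is not a minimisation factor, so any gain from it is a separate benefit of general covariate adjustment. Its size would be a further assumption, and it is not counted here.

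**What to change.** Before unblinding, state in the analysis plan:

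- **Primary estimate:** marginal 28-day mortality risk ratio with 95% CI from a logistic model with standardisation. Covariates are age and PaO2/FiO2 as continuous terms, in line with the article's own argument against categorising, and centre as a random effect, fixed in advance because there are about 50 centres of some 27 patients each.
- **Cox model:** the same covariates, noting that its hazard ratio then becomes conditional on them.
- **Supporting analysis:** the crude risk ratio with its 95% CI, which is what the sample size was built on.
- **Adjustment rule:** replace the imbalance-triggered sentence with this fixed covariate set.
- **Optional:** APACHE II mortality risk as a further pre-specified covariate, justified as prognostic and not by the minimisation.

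The cost is a paragraph of wording and a few lines of code. The article already plans to collect all of these variables, and neither the sample size nor trial conduct changes.

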#### Subgroup analyses

Four subgroup analyses are planned to analyse whether the treatment effect is modified by age, severity of hypoxaemia before randomisation, aetiology of ARDS, or APACHE II score. Subgroup analyses will be conducted for the primary outcome only. It is proposed to replace the APACHE II score with the APACHE II mortality risk, which is calculated from the APACHE II score but also takes into account the underlying condition. APACHE II scores do not correlate well with mortality risk as similar scores may occur in patients with different conditions who have different risks of mortality. This means that APACHE II score is unlikely to be predictive of outcome or of treatment effect. The mortality risk incorporates the underlying condition and is a better measure of a patient's "sickness". It is therefore more plausible that mortality risk could have a treatment-modifying effect, and it is preferable to explore this variable's relationship to treatment effect. However, APACHE II score will be retained in the table of baseline characteristics as a descriptor of the population recruited to the trial. For aetiology of ARDS, the ratio of risk ratios in the direct and indirect aetiology subgroups will be calculated, with its 95% confidence interval [6]. We will not attempt any analysis of subtypes of direct and indirect aetiologies because the number of patients available is too small and there is a risk of misleading results. The other three subgroup-classifying variables are continuous. Although the BALTI-2 protocol specified categorisations for these variables, it is proposed to adopt a different approach because there are problems with categorising continuous variables. First, there is no clear biological rationale behind any cut-points, and attempting to use data-driven procedures to derive "optimal" cut-points is liable to be seriously misleading. Second, there is good evidence that any form of categorisation of continuous variables is potentially misleading, and better methods are available [7,8]. For these reasons, the potential treatment-modifying factors will not be categorised. Instead, we will use a regression approach to model the interaction between the continuous baseline variables and outcomes in each group. Categorisations of age, severity of hypoxaemia and APACHE II score will be retained in the table of participants' characteristics, to facilitate comparison of the randomised groups. If there appear to be baseline imbalances that could affect the comparison between the groups, exploratory analyses will be conducted, adjusting for these.

### Economic Evaluation

Two economic analyses will be undertaken to calculate the expected incremental cost effectiveness of IV salbutamol compared to standard care in the treatment of patients with ARDS, admitted to ICUs in the UK.

A within-trial cost effectiveness analysis comparing the costs and outcomes of patients in each arm of the trial at 12 months. The perspective for this analysis will be that of the NHS and Social Services. The primary outcome for this analysis will be the Quality Adjusted Life Years (QALY's). Utilities will be measured using the EQ-5D at 6 and 12 months follow-up. Within ICU resource use will be identified through a detailed costing study undertaken at a sample of ICUs recruiting to the trial. Use of other hospital services will be abstracted from the trial CRFs. Use of primary, community and social care services will be recorded via a patient diary completed at six and 12 months follow-up. Particular effort will be made to identify place of residence at 12 months follow-up and whether this is funded by health, social services or privately. Out of pocket expenditure and time away from work data will also be collected using the same patient diary. Unit costs will be obtained from national sources such as the NHS reference costs and the PSSRU Unit Costs of Health and Social Care (http://www.pssru.ac.uk/). Where national costs are not available, unit costs will be identified in consultation with finance departments of trusts recruiting to the trial. Parameter uncertainty will be addressed using probabilistic sensitivity analysis. Outputs from the analysis will include the expected incremental cost effectiveness ratio (ICER), a scatterplot on the cost effectiveness plane, cost effectiveness acceptability curve and incremental net benefit assuming lambda = £20,000 per QALY.

As there is potential for a difference in mortality between the groups, a lifetime horizon is required to fully capture the cost and benefits of IV salbutamol compared to usual care. Therefore, we will construct a cost effectiveness model with a lifetime time horizon. This will model the expected long term difference in QALY's lived and health and social care resource utilised by two hypothetical cohorts of patients with ARDS; one treated with IV salbutamol the other not. The age distribution of these cohorts will reflect the age profile of ARDS patients actually seen in UK ICUs. Life expectancy post hospital discharge will be modelled using national age specific life expectancy data adjusted to reflect published evidence on the reduced life expectancy of ICU 'survivors'. Long- term quality of life will be estimated using published age-specific utility data adjusted to reflect any published evidence of a divergence in health related quality of life in ICU 'survivors'. In the absence of evidence to the contrary, the model will assume that the treatment modality does not impact upon the long terms non-ARDS-related health care costs. Costs and outcomes will be discounted in line with best practice recommendations at the time of the analysis. Parameter uncertainty will be addressed using probabilistic sensitivity analysis. Outputs from the analysis will include the expected ICER, a scatterplot on the cost effectiveness plane, cost effectiveness acceptability curve and incremental net benefit assuming lambda = £20,000 per QALY.

